**Sickle cell-specific dose limiting toxicities:**

- Hemolysis:
  - Anemia: >25% decrease in hemoglobin from baseline or  $\leq 5.0$  g/dL; or

- 
- Lactate dehydrogenase increase 3-fold from baseline; or
  - Reticulocyte count increase 3-fold from baseline; or
  - AST increase 3-fold from baseline; or
  - Total bilirubin increase 3-fold from baseline
  - Acute vaso-occlusive episode: within the 6 hour the monitoring window following infusion, an increase in pain over baseline ( $\geq 4$  points on a 10 point pain scale) in the extremities, chest, abdomen or head lasting for at least 2 hours that could not be explained except by sickle cell disease; or
  - Within 72 hours following infusion, a provider encounter (clinic, ED or hospital) for increased pain in the extremities, chest, abdomen or head lasting for at least 2 hours, requiring opioid administration and could not be explained except by sickle cell disease.

**Definition of events not considered as a DLT:**

The following AEs of any grade will not be considered a DLT:

- Chelitis
- Dry Skin
- Nail changes
- Hot flashes/flushes
- SCD associated pain

Decreases in the numbers of iNKT cells is an expected pharmacodynamic response to NKTT120 and will not be considered a DLT.

Acute pVOC and ACS or other SCD-associated AEs (e.g., hemolysis, hepatic/splenic sequestration, decreased haptoglobin, hemoglobinuria, bone pain, chest wall pain, pain in the extremity, priapism in men, gall stones, leg/ankle ulcers, avascular necrosis of bone, stroke, cognitive disabilities) are not unexpected disease-specific events and will not automatically be considered DLT, but will be evaluated on a case-by-case basis and may be elevated to DLT status if warranted and determined to be related to NKTT120.

Episodes of pVOC defined as “crisis” and self-treated by the subject will be recorded in the eDiary and will be recorded as an AE on the CRF, but will not be defined as DLT.

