- If 0 of 3 subjects in the cohort experiences a DLT, escalation to the next dose level cohort may proceed.
- If 1 of 3 subjects in the cohort experiences a DLT, 3 additional subjects will be added to the cohort.
- If  $\geq 2$  of 3 - 6 subjects experience a DLT, the MTD has been exceeded and dose escalation will cease. Three (3) subjects will be added to the previous lower dose cohort(s). The MTD is defined as the highest dose at which no more than one of six subjects experiences a DLT in the dose cohort.

A SRC will review all safety and laboratory data on all subjects in the study at regular intervals. The SRC will also be made aware of any adverse EOs that could be potential DLTs and any SAEs as soon as they are reported. Because of the complex nature of the disease, before any EO is determined to meet DLT criterion, the SRC will meet, ad hoc, to review the safety data for an individual before declaring the event is a DLT or not. While the SRC is determining if a DLT has occurred, no additional subjects will be enrolled.

The SRC will also assess safety signals that may become evident in the longer-term follow-up and will make recommendations to the Sponsor regarding study conduct and risk mitigation, as well as dose de-escalation protocol changes.

Note that peripheral iNKT cells will be followed as a pharmacodynamic marker of drug activity and that depletion of iNKT cells is an expected outcome and will not be considered a DLT. Acute pVOC and ACS or other SCD-associated AEs (e.g., hemolysis, hepatic/splenic sequestration, decreased haptoglobin, hemoglobinuria, bone pain, chest wall pain, pain in the extremity, priapism in men, gall stones, leg/ankle ulcers, avascular necrosis of bone, stroke, cognitive disabilities) will not automatically be considered DLT, but will be evaluated on a case-by-case basis and may be elevated to DLT status if warranted and related to NKTT120. This decision will be made by the SRC.

The primary endpoint (MTD or RDL) will be completed when the last subject dosed completes dosing plus two weeks of follow-up (time at which next cohort would have started). However, each subject will be followed until 1 month after their iNKT cells have returned to detectable levels. If the highest dose level is reached without determining a MTD, the RDL(s) for phase 2 will be determined by a dose that is at or below the highest dose and which is associated with iNKT cell recovery that allows dosing every 4-6 months in phase 2 studies.

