#### **6.6.1. Safety Criteria for Adjustment or Stopping Doses**

DLT will be evaluated for each subject during the two-week interval following dosing. This interval will allow identification of any acute, dose-limiting events that will determine dose-escalation or expansion of dose-level cohorts. All EOI will be reviewed by the SRC to determine if they are a DLT.

Subjects who experience a DLT will remain in the study to complete the safety evaluations and follow-up until resolution or stabilization of the DLT. All AEs and SAEs will be determined and graded for intensity based on CTCAE criteria. AEs and SAEs will be determined to be

dose-limiting if they occur during the first two weeks post-dosing and meet the criteria described below.

All safety data, including adverse events and laboratory abnormalities, will be reviewed by the SRC periodically in order to assist the sponsor in evaluating potential safety signals during the follow-up until iNKT cells recover.

**Definition of DLT:** a DLT is defined only for adverse events that occur within 2 weeks of dosing (with the exception of any acute vaso-occlusive episode).

Any adverse event grade 3 or higher on NCI CTCAE version 4.03 will be considered an EOI and a potential dose limiting toxicity.

All adverse EOI below that could be dose-limiting toxicities will be reviewed immediately by the SRC to determine if they constitute a DLT. All serious adverse events at any time will be reviewed by the SRC so that the SRC can make recommendations to the Sponsor regarding dosing cohorts.

**Definition of EOI:** an EOI is defined only for adverse events that occur within 2 weeks of dosing (with the exception of any acute vaso-occlusive episode). Any adverse event grade 3 or higher on NCI CTCAE version 4.03 will be considered an EOI.

Additionally, the following study and disease-specific toxicities will be considered an EOI and evaluated to determine if a DLT has been experienced:

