- **Acute vaso-occlusive episode:** within the 6-hour monitoring window following infusion, an increase in pain over baseline ( $\geq 4$  points on a 10 point pain scale) in the extremities, chest, abdomen or head lasting for at least 2 hours that could not be explained except by sickle cell disease.
- **Increased pain in the extremities, chest, abdomen or head lasting for at least 2 hours:** Within 72 hours following infusion, a provider encounter (clinic, ED or hospital), requiring opioid administration and could not be explained except by sickle cell disease.

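### Section 6.6.1 sends acute vaso-occlusive pain for DLT adjudication and also lists sickle pain of any grade, without qualification, as never a DLT

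*Protocol*

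**What the plan says.** Three sets of statements in the protocol bear on sickle pain.

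- **Adjudicated.** Section 6.6.1 states that "the following study and disease-specific toxicities will be considered an EOI and evaluated to determine if a DLT has been experienced". Under its heading for sickle cell-specific dose-limiting toxicities it gives two pain criteria. The first is a rise of at least 4 points on a 10-point scale, lasting at least 2 hours, within the 6-hour monitoring window. The second is a provider encounter within 72 hours for increased pain lasting at least 2 hours, "requiring opioid administration and could not be explained except by sickle cell disease". The first criterion carries the same requirement that only sickle cell disease explains the pain. Section 11.1 repeats both as events of interest; the second reads "Within 72 hours following infusion, a provider encounter (clinic, ED or hospital), requiring opioid administration".
- **Eligible if drug-related.** Section 6.1 says that acute pVOC, bone pain, chest wall pain and pain in the extremity, among other disease events, "may be elevated to DLT status if warranted and related to NKTT120", and gives that decision to the SRC. The part of Section 6.6.1 on events not considered DLTs repeats the rule: such events "may be elevated to DLT status if warranted and determined to be related to NKTT120". Section 11.3 rules out only disease-specific events not thought to be related to the drug.
- **Excluded outright.** That same part of Section 6.6.1 opens with "The following AEs of any grade will not be considered a DLT". Its list includes "SCD associated pain", beside cheilitis, dry skin, nail changes and hot flashes. The term is not defined and nothing says which rule prevails.

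**The concern.** Pain that meets either criterion in Section 6.6.1 must be explainable only by sickle cell disease. It is therefore sickle-associated pain by the protocol's own definition, and the bullet covers it. One rule sends the event to the SRC for a DLT decision, while the other settles that decision in advance as no.

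The DLT count determines escalation, cohort expansion and the MTD, which is one of the two forms of the primary endpoint. Acute vaso-occlusive pain is also a toxicity the protocol singles out. Section 4.9 justifies the two-week interval partly by the effect of rapid iNKT depletion on sickle cell disease, and it names vaso-occlusive episodes and opioid-treated pain encounters among the dose-limiting toxicities the SRC is to evaluate. In a first-in-human study, two people applying the same text could reach different DLT counts, and so different MTDs, from the same data.

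**Working it through.** **Step 1. Does the overlap exist?** Take a subject with an opioid-treated clinic encounter for chest pain 48 hours after infusion, lasting more than 2 hours, explained only by sickle cell disease and judged by the SRC to be related to NKTT120.

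| Rule | Result |
|---|---|
| Section 6.6.1, sickle cell-specific criteria | Event of interest, adjudicated for DLT |
| Sections 6.1 and 6.6.1, case-by-case rule | May be elevated to DLT, because related |
| Section 11.3 | Not ruled out, because related |
| Section 6.6.1, bullet on sickle pain | Not a DLT at any grade |

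Three rules leave the event eligible and one bars it.

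**Step 2. Effect on the 3+3 decision, with no assumed rate.** Under Section 6.1, after 0 of 3 DLTs "escalation to the next dose level cohort may proceed"; after 1 of 3, three subjects are added; with 2 or more among 3 to 6, the MTD is exceeded. Suppose the only candidate DLTs in a cohort of three are drug-related pain events that meet the criteria and that the SRC would elevate.

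| Subjects with such pain | Pain counted | Bullet applied literally |
|---|---|---|
| 1 of 3 | 1/3: add three subjects | 0/3: escalation may proceed |
| 2 of 3 | 2/3: MTD exceeded | 0/3: escalation may proceed |

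**Step 3. Reproduce the plan's operating characteristics.** For a true DLT probability p, with q = 1 − p, a dose is escalated after 0/3, or after 1/3 followed by 0/3:

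Pr(escalate) = q³ + 3pq² × q³ = q³ + 3pq⁵.

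This gives 0.973, 0.906, 0.709 and 0.172 at p = 0.05, 0.10, 0.20 and 0.50, as in Table 5. Nine of the ten rows reproduce as printed. The last, printed as p = 0.09, fits only p = 0.90; that is a separate matter.

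**Step 4. Illustration under assumed rates.** The protocol gives no rate for drug-related pain or for other DLTs. Assume other DLTs at 5%, independent of pain DLTs at rate b. The combined rate is p = 1 − 0.95(1 − b). With pain excluded, p = 0.05 and Pr(escalate) = 0.973.

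| Assumed pain-DLT rate b | Combined p | Pr(escalate), pain counted | Gap from 0.973 |
|---|---|---|---|
| 5% | 0.0975 | 0.910 | 0.06 |
| 10% | 0.145 | 0.824 | 0.15 |
| 20% | 0.240 | 0.622 | 0.35 |
| 30% | 0.335 | 0.425 | 0.55 |

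With other DLTs assumed at 10%, the figure is 0.906 with pain excluded, against 0.824, 0.730, 0.536 and 0.360 at the same four pain rates. These values treat escalation as automatic once the count allows it, as Table 5 does.

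**The case against.** The strongest reply is that the intended rule can be recovered from the text. The bullet sits among trivial events. The elevation rule a few lines below names acute pVOC and several types of pain. The separate sentence excluding self-treated crises would be redundant if all sickle pain were already excluded. Read whole, the section points to background pain as the intended meaning. That is probably right, but the limit is not written, and the words on grade extend the exclusion to severe pain. The argument supports adding the limit.

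Second, there are safeguards. The SRC reviews every event of interest and enrolment pauses while it decides (Section 6.1). Escalation after 0/3 is permitted, not required, and the sponsor decides with committee input (Study Design Notes). If no MTD is reached, the RDL rests on the overall safety profile and the duration of iNKT depletion (Synopsis; Section 12), which takes in pain whether or not it is labelled a DLT. All of this stands. A reader might infer that the bullet forces escalation, strips the SRC of all discretion or undermines the whole primary endpoint. The documents do not support that: the elevation rule is in the same part of Section 6.6.1, and only the MTD branch depends strictly on the DLT count. The safeguards do not, however, correct that count if the bullet is followed.

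Third, the size is unknown. A reader might try to anchor it in the 1 to 3.5 pVOC episodes per subject-year given in Section 4.3. At a constant rate this means 1 − exp(−3/365) = 0.8% to 1 − exp(−3.5 × 3/365) = 2.8% of subjects with an episode in any 72 hours. That is not a measure of the conflict. Background episodes are unrelated to the drug, so under Section 11.3 they are not DLTs on either reading. The rate is also a general one, whereas enrolled subjects must have had no medically treated crisis in the preceding month.

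**Conclusion.** The contradiction is certain: Section 6.6.1 both adjudicates and bars the same events, with no order of precedence. Its consequence is conditional. It changes the DLT count only if drug-related vaso-occlusive pain occurs and the bullet is applied literally; then two affected subjects of three are recorded as 0/3 instead of 2/3. The escalation probabilities show how sensitive the rule is, but they rest wholly on assumed rates and on independence of pain and other DLTs. They do not estimate what will happen in this trial. The point should be fixed because the wording governs a safety count in a first-in-human study and the correction costs almost nothing.

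**What to change.** In Section 6.6.1, under events not considered a DLT, replace the sickle pain bullet with: *SCD associated pain that does not meet the acute vaso-occlusive episode criteria above and is not judged by the SRC to be related to NKTT120*. Pain that meets the criteria then goes to the SRC, drug-related pain stays eligible, and unrelated background pain stays excluded, in line with Sections 6.1, 11.1 and 11.3. The sentence on self-treated crises can remain as it is.

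The amendment should not go on to tie the repeated exception for acute vaso-occlusive episodes (Sections 6.6.1, 11.1, 11.2.1.1 and 12), or the wording of Section 4.9, to the 6-hour and 72-hour windows. That could be read as barring vaso-occlusive pain on days 4 to 14 from DLT review. Sections 6.1 and 6.6.1 allow that review: the elevation rule has no 72-hour limit, and any grade 3 or higher event within two weeks is an event of interest.

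The cost is one line in a protocol amendment, with no added subjects, visits or assessments.

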**6.7. Criteria for Study Termination**

NKTT and the Investigator reserve the right to terminate this study at any time. In terminating the study, NKTT and Investigator will assure that adequate consideration is given to the protection of the subjects’ safety and interests. This is an open-label study and review of subject safety outcomes will be made on an ongoing basis.

---

**6.7.1. Stopping Rules**

Enrollment in the study will be stopped and administration of NKTT120 will be halted for all newly enrolled subjects if the SRC detects a potential life-threatening safety signal during the study, including during the long-term follow-up of the subjects, and notifies the sponsor that they recommend stopping of dosing of any additional subjects. Adverse events will be evaluated to determine if they are unanticipated effects of the treatment. These events include, but are not limited to:

1. Serious, medically important or opportunistic infections requiring treatment with parenteral antibiotics (and/or empirical use of antibiotics when subject is admitted to hospital or emergency department for pVOC or other event)
2. Cancers of type or rate unexpected in the adult SCD population.

This is a single dose study, and once enrolled and dosed, subjects cannot be considered removed from study, and all attempts must be made to follow the subject for safety reasons.

**Figure 1: Study Schematic**

[figure not shown]

**Study Design Notes**

- 2-30 subjects
- NKTT will make dose escalation decisions with input from Scientific Review Committee
- MTD or RDL will not be complete until the last subject dosed in a cohort completes dosing plus two weeks of follow-up
- All subjects will be followed until 1 month AFTER their iNKT cells have returned to detectable levels
- If highest dose level is reached without determining a MTD, then the RDL for Phase 2 will be the dose that is at or below the highest dose and which iNKT cell recovery will allow dosing every month or every other month in Phase 2 study

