| 
Criteria for evaluation:
 
Pharmacokinetics: The PK objective is to determine the PK profile of NKTT120, the relationship of PK to depletion and recovery of iNKT cells, the adverse event (AE) profile and presence of ADAs.
 
Pharmacodynamics: The PD objective is to determine the profile of iNKT cell depletion and recovery after dosing with NKTT120 and to correlate the PK and PD profiles. It is anticipated that iNKT cells will recover after NKTT120 is eliminated from or is present at very low concentrations in the serum.
 
Safety:
 
Only one subject will be dosed on any day. Subjects will be monitored in the clinical trial center
                                                                                                                                                                                                                              |

immediately before and for at least 6 hours after each dose for acute toxicity (i.e., infusion reactions or cytokine release syndrome). Subjects will not be discharged from the clinical trials center if they are not stable at 6 hours post-dosing. Subjects will return for follow-up safety monitoring and to have blood drawn for PK, hematology and chemistry assessments per the protocol schedule of evaluations (Table 3). These PK and PD assessments require frequent monitoring until recovery of iNKT cells (Table 3). Monthly monitoring will include: assessment of AEs, change in medications, symptom-directed physical examinations, vital signs, medication review, hematology profile, lymphocyte subsets (including iNKT cells and their activation state), chemistry profile, liver function tests, prothrombin time (PT), and activated partial thromboplastin time (aPTT) (Table 3). Subjects will have blood drawn for analysis of iNKT cell numbers monthly until recovery. Adverse events will be graded for severity using the CTCAE v.4.03 with modifications for SCD and presented by body system and relationship to NKTT120.

The Safety Review Committee (SRC) will immediately review all adverse Events of Interest (EOI) that might be dose limiting toxicities (DLT) to determine if they do, in fact constitute a DLT. The SRC will also review serious adverse events (SAEs) reported for all subjects in the study, as well as all safety and laboratory data at regular intervals to assess emergent safety signals during longer-term follow-up post-dosing.

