#### **Statistical methods:**

Primary outcome: Maximum tolerated dose (MTD) is defined as the dose level that is estimated to produce DLT in < 33% of subjects in a cohort using a 3+3 design. If no MTD is achieved, the RDL will be determined based on the overall safety profile of NKTT120 and the duration of iNKT cell depletion.

Secondary outcome: Non-compartmental pharmacokinetic parameters--peak concentration ( $C_{max}$ ), minimum concentration ( $C_{min}$ ), average concentration ( $C_{avg}$ ), area under the time-concentration curve (AUC), half-life ( $t_{1/2}$ ), volume of distribution ( $V_d$ )--will be calculated for all subjects. Descriptive statistics of these parameters will be provided by dose level.

Descriptive statistics of the PK/PD (peripheral iNKT cell subset/T cell (TC) ratio depletion and recovery to quantifiable levels) will be provided by dose level. PK/PD will be examined for association with AEs, pain scores and other endpoints, and changes in biomarkers.

Demographics and baseline status will be documented by dose level and/or overall, as applicable.

Descriptive statistics of change in pain score, analgesic use, peak expiratory flow, and shortness of breath will be collected by eDiary and/or during clinic visits. The Quality of Life (QoL) assessments will be collected at clinic visits and will be compared to pre-treatment screening run-in values. Trends in improvement or deterioration in these values with treatment and across the dose-level cohorts will be described.

Descriptive statistics of change from screening in serum and cellular biomarkers of inflammation, coagulation, and endothelial function will be provided.

ADAs will be described as present or absent and correlated with NKTT120 serum concentrations and iNKT cell recovery. Numbers of subjects with positive tests for ADAs per cohort and per study will be reported.

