## **5. TRIAL OBJECTIVES AND PURPOSE**

### **5.1. Primary objective**

The primary objective is to assess the safety and MTD, or RDL for Phase 2, of a single ascending dose of IV NKTT120 in adult subjects with stable SCD. If the highest dose level is reached without determining a MTD, the RDL(s) for phase 2 will be determined by a dose that is at or below the highest dose and which is associated with iNKT cell recovery that allows dosing every 4-6 months in phase 2 studies.

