## **6.2. Study Duration and Visit Schedule**

Enrollment through follow-up is estimated to require 18 months. The study continues until MTD has been determined or the upper dose limit of this protocol has been reached without determining the MTD. The dose-level cohort that represents the RDL will be expanded to 6 subjects to confirm the RDL.

All study assessments by visit are defined in the [Table 3](#) and safety assessments in Section 11.

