### Escalation scheme

Five dose levels of NKTT120 will be assessed. Each dose level will be administered as a single ascending IV dose. The dose levels to be investigated are 0.001, 0.003, 0.01, 0.03 and 0.1 mg/kg.

A standard dose escalation Fibonacci 3+3 design will be employed. Initially, three subjects will be treated. If no subject experiences DLT, dosing will escalate. If one subject experiences DLT, 3 additional subjects will be treated at the current dose and escalation will occur only if no more than 1 of 6 subjects experiences DLT. If  $\geq 2$  of 3 - 6 subjects experiences DLT at the initial dose level of 0.001 mg/kg, then it may be de-escalated. The study continues until MTD has been determined, or the highest dose cohort is filled. If no MTD is reached, RDL will be determined based on the overall safety profile of NKTT120 and the duration of iNKT cell depletion. The RDL(s) for phase 2 will be determined by a dose that is at or below the highest dose tested which is associated with timing of iNKT cell recovery that allows dosing every 4-6 months in phase 2 studies. The dose-level cohort that represents the RDL will be expanded to 6 subjects to confirm the RDL. [Table 5](#) below provides the probability of dose escalation.

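### The Study Design Notes under Figure 1 give the RDL rule a Phase 2 interval of one to two months; Sections 5.1, 6.1, 6.3.1 and 12 all give 4-6 months

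*Protocol*

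**What the plan says.** The primary endpoint (Section 6.3.1) is the MTD or, if none is found by the highest dose, the RDL. For that fallback, Section 5.1 asks for a dose at or below the highest one that is "associated with iNKT cell recovery that allows dosing every 4-6 months in phase 2 studies". Sections 6.1 and 6.3.1 repeat this wording. The escalation scheme in Section 12 has the same interval: "associated with timing of iNKT cell recovery that allows dosing every 4-6 months in phase 2 studies".

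The Study Design Notes beneath Figure 1 set the same condition (highest dose reached, no MTD) and the same bound (at or below the highest dose), but choose the dose for which "iNKT cell recovery will allow dosing every month or every other month in Phase 2 study".

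The synopsis, under statistical methods, gives no interval: "the RDL will be determined based on the overall safety profile of NKTT120 and the duration of iNKT cell depletion". On what follows from the choice, Section 6.2 says: "The dose-level cohort that represents the RDL will be expanded to 6 subjects to confirm the RDL".

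**The concern.** The interval is the only stated recovery criterion for picking the RDL, and the protocol gives two values for it. The choice has consequences inside this trial as well as for Phase 2, because the chosen cohort is enlarged to 6 subjects.

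Reaching the top dose without an MTD is a realistic outcome. Section 4.4 reports no adverse events in monkeys at exposures more than 100-fold above the highest expected here, and Section 4.8 puts the top dose at one third of the maximum recommended safe dose. Someone working from the notes beside the study schematic could therefore pick and expand a different cohort from someone working from Section 5.1 or Section 12.

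**Working it through.** No design figure needs reproducing; this is a comparison of texts with simple arithmetic.

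**Every statement of the rule**

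| Place | Phase 2 interval |
|---|---|
| Section 5.1, primary objective | every 4-6 months |
| Section 6.1, overall design | every 4-6 months |
| Section 6.3.1, primary endpoint | every 4-6 months |
| Section 12, escalation scheme | every 4-6 months |
| Figure 1, Study Design Notes | every 1 or 2 months |
| Synopsis, statistical methods | none given |

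**Distance between the intervals**

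- Overlap of 1-2 and 4-6 months: none.
- Gap: 4 − 2 = 2 months.
- Ratio: from 4/2 = 2 to 6/1 = 6.
- In weeks, at 365.25/12/7 weeks per month: 4.3-8.7 against 17.4-26.1.

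**Can the data tell the rules apart?** The synopsis (criteria for evaluation, Safety) says: "Subjects will have blood drawn for analysis of iNKT cell numbers monthly until recovery". A 2-month gap is therefore two scheduled visits, so they can.

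**Does the answer depend on what it means for recovery to allow an interval?** The protocol does not define this. Let T be the month of recovery.

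| Reading | 4-6 month rule | 1-2 month rule | A value of T that separates them |
|---|---|---|---|
| Recovery matches the interval | 4 ≤ T ≤ 6 | 1 ≤ T ≤ 2 | T = 4: meets the first, fails the second |
| Recovery no later than the interval | T ≤ 4 (or 6) | T ≤ 1 (or 2) | T = 4: 4 ≤ 4 holds, 4 ≤ 2 does not |
| Depletion lasts at least the interval | T ≥ 4 (or 6) | T ≥ 1 (or 2) | T = 3: 3 ≥ 2 holds, 3 ≥ 4 does not |

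The rules differ on all three readings. Only the recovery times that separate them change.

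**Could this separate the planned doses?** The protocol's own expectations suggest so. In monkeys, cells were measurable again at 5 weeks after 0.01 mg/kg and 8 weeks after 0.03 mg/kg (Section 4.4), both within 4.3-8.7 weeks. In humans at 0.1 mg/kg, return could take 6 months or more (Section 6.2.2), at or beyond the top of the 4-6 month range. The monkey times are not converted to human times here, so this is illustration only.

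**The case against.** The strongest reply is that the practical effect is small. The RDL does not follow mechanically from the interval: overall safety counts too, the protocol allows more than one RDL, and escalation and DLT decisions never use the interval. A careful reader would follow the objective, design, endpoint and statistics sections over notes to a figure. This stands, and it limits the weight of the point. It does not remove the conflict, because the notes are current text and give a different threshold for the same decision.

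A second reply is that the lack of overlap describes the stated intervals and not necessarily the sets of qualifying doses. If recovery need only occur by the interval, a dose recovering by month 2 meets both rules. If depletion must last at least the interval, recovery at month 4 can meet both. Both observations are right. They change which cohorts are affected, but on each reading some recovery times pass one rule and fail the other.

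Third, Sections 5.1, 6.1 and 6.3.1 share essentially one sentence, so their agreement is not independent confirmation. That is fair. However, Section 12 words the rule separately and gives the same interval, and Section 4.3 envisages a treatment given relatively infrequently. The sponsor can settle the intended interval when making the correction.

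**Conclusion.** The inconsistency is real and should be fixed. The two intervals are 2 months apart and differ 2- to 6-fold, on a criterion that helps decide the fallback primary endpoint and which cohort is expanded to 6 subjects. It matters only if no MTD is found, and only for cohorts whose recovery time falls where the rules disagree. The size of any resulting dose difference cannot be derived from the protocol. That the notes are the wrong text is a judgement from the agreement of the objective, design, endpoint and statistics sections. No sample size or error rate is affected.

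**What to change.** In the last bullet of the Study Design Notes under Figure 1, replace the monthly or every-other-month interval with every 4-6 months, so that it matches Sections 5.1, 6.1, 6.3.1 and 12. The sponsor should confirm 4-6 months as the intended interval when making the change. The cost is a one-line wording correction; visits, sampling, follow-up and the trigger for the end-of-study visit stay as they are.
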